# Microfragmented Fat and Biphasic Calcium Phosphates for Alveolar Cleft Repair: Protocol for a Prospective, Nonblinded, First-in-Human Clinical Study

**DOI:** 10.2196/42371

**Published:** 2024-01-15

**Keywords:** microfragmented fat, calcium phosphate, bone regeneration, regenerative medicine, alveolar, bone grafting, bone, graft, alveolar cleft, surgery, surgical, perioperative, mouth, oral surgery, maxillofacial, jaw, oral pathology, oral, dentistry, dental, tooth, teeth, osteo, osteoconductive biphasic calcium phosphate, autograft, operation

## Abstract

**Background:**

Biphasic calcium phosphates (BCP) may serve as off-the-shelf alternatives for iliac crest-derived autologous bone in alveolar cleft reconstructions. To add osteoinductivity to the osteoconductive BCPs to achieve similar regenerative capacity as autologous bone, a locally harvested buccal fat pad will be mechanically fractionated to generate microfragmented fat (MFAT), which has been shown to have high regenerative capacity due to high pericyte and mesenchymal stem cell content and a preserved perivascular niche.

**Objective:**

Our primary objectives will be to assess the feasibility and safety of the BCP-MFAT combination. The secondary objective will be efficacy, which will be evaluated using radiographic imaging and histological and histomorphometric evaluation of biopsies taken 6 months postoperatively, concomitant with dental implant placement.

**Methods:**

Eight patients with alveolar cleft (≥15 years) will be included in this prospective, nonblinded, first-in-human clinical study. MFAT will be prepared intraoperatively from the patient’s own buccal fat pad. Regular blood tests and physical examinations will be conducted, and any adverse events (AEs) or serious EAs (SAEs) will be meticulously recorded. Radiographic imaging will be performed prior to surgery and at regular intervals after reconstruction of the alveolar cleft with the BCP-MFAT combination. Biopsies obtained after 6 months with a trephine drill used to prepare the implantation site will be assessed with histological and histomorphometric analyses after methylmethacrylate embedding and sectioning.

**Results:**

The primary outcome parameter will be safety after 6 months’ follow-up, as monitored closely using possible occurrences of SAEs based on radiographic imaging, blood tests, and physical examinations. For efficacy, radiographic imaging will be used for clinical grading of the bone construct using the Bergland scale. In addition, bone parameters such as bone volume, osteoid volume, graft volume, and number of osteoclasts will be histomorphometrically quantified. Recruitment started in November 2019, and the trial is currently in the follow-up stage. This protocol’s current version is 1.0, dated September 15, 2019.

**Conclusions:**

In this first-in-human study, not only safety but also the histologically and radiographically assessed regenerative potential of the BCP-MFAT combination will be evaluated in an alveolar cleft model. When an SAE occurs, it will be concluded that the BCP-MFAT combination is not yet safe in the current setting. Regarding AEs, if they do not occur at a higher frequency than that in patients treated with standard care (autologous bone) or can be resolved by noninvasive conventional methods (eg, with analgesics or antibiotics), the BCP-MFAT combination will be considered safe. In all other cases, the BCP-MFAT combination will not yet be considered safe.

**Trial Registration:**

Indonesia Clinical Trial Registry INA-EW74C1N; https://tinyurl.com/28tnrr64

**International Registered Report Identifier (IRRID):**

DERR1-10.2196/42371

## Introduction

Alveolar cleft is defined as a bone gap in the primary palate from the nasal sill to the incisive foramen [1]. The defect occurs as a result of disruption of primary palate development between 4 and 12 weeks of gestational age, specifically in the frontonasal prominence [2]. The treatment protocol varies on the basis of the following factors: timing, surgical procedure, and grafting material. Secondary alveolar bone grafting (SABG) is the most preferred and successful method that is usually performed during the mixed dentition period (6-11 years), which allows the provision of support to teeth eruption and facial growth [1]. The iliac crest as a bone graft donor for alveolar cleft reconstruction has gained popularity since it was first introduced by Schmid [3] in 1954, and, in particular, for SABG procedures because it allows harvesting of large amounts of bone for alveolar cleft surgery [4]. Other bone graft sources include the cranium, tibia, and the mandibular symphysis [5]. However, several studies have reported risks of general postoperative complications using autografts, such as pain, prolonged hospital stay, and donor site–specific complications such as scarring, cutaneous nerve injury near the iliac crest, and hematoma after harvesting the cranial bone [6-9]. Therefore, alternative materials are being evaluated for alveolar cleft surgery.

Biphasic calcium phosphate (BCP) is a bioceramic that consists of 2 materials, hydroxyapatite (HA) and β-tricalcium phosphate, mixed in different ratios [10]. It is a biocompatible, easy-to-handle, safe material with a mineral composition comparable to that of human bone tissue [10]. BCP has been mixed in vivo and in vitro with autografts, inducing factors or cells to improve its osteoinductivity [11,12], also in the fields of dentistry and maxillofacial surgery [13-15]. Although calcium phosphate ceramic is not yet considered standard-of-care, it has been used for alveolar cleft reconstruction with satisfactory results [16], reportedly providing support for teeth eruption [17].

Adipose tissue is a source of mesenchymal stem cells, and adipose stem cells (ASCs) can be collected with minimum risk and discomfort from the buccal fat pad (BFP) [18]. The BFP surrounds the buccinators muscle and other superficial muscles such as the masseter, the zygomaticus major, and the zygomaticus minor [19]. Moreover, multiple studies have shown that the cell yield of ASCs per volume is at least 100-500 times that of mesenchymal stem cells in bone marrow aspirates [18,20]. Commonly, ASCs are prepared using enzymatic (collagenase) digestion which, however, is considered “more than minimal manipulation” of the cells by the US Food and Drug Administration and the European Medicines Agency [21]. An alternative method, which also takes considerably less time, involves processing the adipose tissue mechanically into microfragmented fat (MFAT) [22]. MFAT is reported to have similar or even higher secretory activity of regenerative growth factors and cytokines and pericyte content than an enzymatically derived stromal vascular fraction (SVF) [23]. In addition, the MFAT procedure can be applied even in regular hospitals because its harvesting and processing does not require a major invasive surgery, specialized equipment or expensive disposables, or good manufacturing practices–qualified cell culture expansion. Autologous application of MFAT has, among others, been used with success for clinical reconstructions in the maxillofacial area [24].

We hereby describe the protocol of a first-in-human clinical safety trial using BCP mixed with MFAT for alveolar cleft reconstruction. Our hypothesis is that the combination will be a safe, efficient, and effective alternative to conventional autograft since the osteoconductive BCP is supplemented by the regenerative capacity from the MFAT.

## Methods

### Study Design

This first-in-human surgical study can be classified as a “stage 1” study in accordance with the IDEAL (innovation, development, exploration, assessment, and long-term study) framework [25]. It is a single-center prospective clinical trial comprising 8 patients, assessing the safety of a combination of MFAT and BCP (BoneCeramic, Straumann) as bone graft material for alveolar cleft reconstruction. The BCP is a synthetic bone graft containing 60% HA and 40% β-tricalcium phosphate, a porosity of 90%, and an interconnected pore size of 100-500 µm. The BCP will be combined in a 1 g:1 cm^3^ ratio with MFAT prepared from the patients’ own BFP, which is processed with a 1.2-mm single-use sizing transfer Tulip Gen II Nanofat Kit (Tulip Medical). The primary end point will be set at 6 months. At each follow-up visit, adverse events (AEs) or serious AEs (SAEs) will be documented, and clinical assessments will be performed at time points specified in the *Interventions* section. After these 6 months, a bone biopsy sample will be taken using a hollow drill during dental implant preparation and subsequently processed for histological or histomorphometric analysis (Figure 1). Finally, a report on safety and proof of concept with regard to bone formation will be made and published.

**Figure 1 figure1:**
[figure not shown]
Simplified diagram of the study protocol (adapted from the SPIRIT [Standard Protocol Items: Recommendations for Interventional Trials] checklist; Multimedia Appendix 1). BCP: biphasic calcium phosphate; MFAT: microfragmented fat.

### Ethical Considerations

The clinical trial protocol was approved by the ethical committee of Hasanuddin University, Makassar, Indonesia (1063/UN4.6.4.5.31/PP36/2019) and registered in the Indonesian trial registry (INA-EW74C1N). Informed consent will be obtained from candidates or their parents or legal guardians who are willing to join the trial after being fully educated about the trial procedure. This study complies with the principles of the Declaration of Helsinki. In the informed consent form signed by the patients or their legal representatives, consent to publish their data in a deidentified manner is included.

### Inclusion and Exclusion Criteria

Patients will be included on the basis of the following criteria [26]: being healthy male or female participants aged ≥15 years, having unilateral alveolar cleft without any previous history of grafting procedures, being categorized as normal healthy patients for anesthetic risk per the American Society for Anesthesiologists’ criteria, and having a normal blood count.

Patients will be excluded on the basis of the following criteria [26]: having poor oral hygiene with mouth plaques; having systemic disease; having systemic or local infection; having received chemotherapy, radiotherapy, immunosuppressives, or anticoagulants that may interfere with the healing process; having received bone growth–inducing factors, malnutrition, or active influenza; and being pregnant.

### Interventions

Under general anesthesia and infiltration with lidocaine (1%) with epinephrine (1:100,000 dilution), the surgeon will identify the Stensen’s duct with a lacrimal probe and make an incision 2-3 cm below the duct [27].﻿ A dissection penetrating the muscles and the superficial fascia will allow spontaneous herniation of the BFP [27]. This procedure will be carried out bilaterally on both cheeks in order to obtain approximately 3 cm^3^ of fat. After vasoconstrictor infiltration with epinephrine (1:100,000), a full mucoperiosteal flap spanning the first molar to the central incisor is lifted. After exposure of the full alveolar cleft and to separate the nasal layer from the oral mucosa, the tissue was meticulously dissected. Following the reflection of a palatal mucoperiosteal flap from either side of the cleft, the palatal tissues are elevated. The oronasal fistula is repaired cranially by elevating and suturing the nasal mucosa [4], thereby creating a pocket for BCP-MFAT deposition.

In parallel with the defect surgery, the harvested fat will be chopped into small pieces with a scissor and soaked in normal saline for 10-15 minutes. The normal saline then will be drained and the chopped fat will be processed into MFAT using 2 syringes (size 10 cm^3^) connected with the 1.2-mm single-use sizing transfer Tulip Gen II Nanofat Kit in accordance with the manufacturer’s protocol. MFAT will be mixed with BCP (Straumann Bone Ceramic) in a ratio of 1 g:1 cm^3^ until it reaches homogenous consistency. The BCP-MFAT mixture will be placed as a graft material into the alveolar cleft defect. If the defect is large and requires more bone graft, another mixture will be prepared with the same mixing ratio. If necessary, a membrane will be used to cover the grafted defect. Finally, the defect will be closed by suturing the palatal mucoperiosteal flaps using absorbable sutures with 3-0 vicryl sutures for mucosa and 4-0 vicryl sutures for nasal reconstruction. All patients will be prescribed antibiotics and analgesics postoperatively.

### AE Assessment

Any change in the health of subjects will be documented in their medical history, and required medical care will be provided. Any unexpected physical or laboratory change, symptom, or disease that occurs in a treated patient who has been administered the graft will be documented as an AE. An AE will be graded in accordance with the World Health Organization’s classification [28] as either serious or nonserious based on its intensity. The Clavien-Dindo Classification of Surgical Complications will also be used in case of any incidence [29]. In the case of an SAE, a report will be made to the sponsor within 24 hours and to the ethical committee within 3 days from the date of onset. If the SAE concerns severe toxicity or infection associated with graft products, the trial will be terminated immediately.

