### Recruitment

Patients will be recruited from an existing database of the Hasanuddin University Dental Hospital, from general practices of Hasanuddin Dental Hospital and in the area around Makassar. Thereafter, we will determine whether the candidates fulfill the study’s inclusion and exclusion criteria. Thorough assessment and training regarding the safety measurements at the research site at Hasanuddin University Dental Hospital will be performed prior to the trial by the ethical and surgical teams.

Since we did not want to enroll children in a safety study with this novel concept in clinical practice, we chose to only include older adolescent and adult patients, being themselves capable of decision-making. Within Indonesia, this age group is more common due to cultural and religious backgrounds causing abstinence from cleft surgeries.

The trial will be conducted at Hasanuddin Dental Hospital. All participants will be asked to sign an informed consent form after risks and possible complications of the procedure (eg, bleeding, infection, cheek asymmetry, parotid duct injury, possibility of facial nerve branches injury, and—although not likely—nonclosure) were appropriately communicated with the patient. Data will be handled and stored in a coded—that is, deidentified—format, so that data cannot be traced back to the patient without a decoding key, which is stored in a locked place and only accessible to the study’s principal investigator. Implants will be offered free of charge.

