## Results

The primary outcome parameter will be safety after 6 months’ follow-up, assessed by closely monitoring possible occurrences of AEs or SAEs, radiographic imaging, blood tests, and physical examinations. For efficacy, radiographic imaging will be used for clinical grading of the bone construct using the Bergland scale. In addition, bone parameters such as bone volume, osteoid volume, graft volume, and number of osteoclasts will be histomorphometrically quantified. We expect that the feasibility and safety of the procedure will be apparent, as well as its initial efficacy. Recruitment started in November 2019, and the trial is currently in the follow-up stage. This protocol’s current version is 1.0, dated September 15, 2019.

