## Abbreviations

AE: adverse event
ASC: adipose stem cell
BCP: biphasic calcium phosphate
BFP: buccal fat pad
HA: hydroxyapatite
IDEAL: innovation, development, exploration, assessment, and long-term study
MFAT: microfragmented fat
SABG: secondary alveolar bone grafting
SAE: severe adverse event
SVF: stromal vascular fraction

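### Seriousness is decided by intensity, and AEs are limited to unexpected changes in grafted patients, so the events behind the safety verdict can be misclassified or left uncounted

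*Protocol article*

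**What the plan says.** AE Assessment in the protocol article sets two rules.

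- **What counts.** An AE is defined as follows: "Any unexpected physical or laboratory change, symptom, or disease that occurs in a treated patient who has been administered the graft". The sentence before it sends every change in health to the medical history.
- **What is serious.** An AE is graded under a cited WHO classification "as either serious or nonserious based on its intensity". Clavien-Dindo grading is added but is not tied to the serious/nonserious decision.

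The abbreviation list reads "SAE: severe adverse event", whereas Study Design says "adverse events (AEs) or serious AEs (SAEs) will be documented".

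Recruitment lists what patients are told may happen: "bleeding, infection, cheek asymmetry, parotid duct injury, possibility of facial nerve branches injury", and, as unlikely, nonclosure.

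The primary outcome is safety at 6 months. The abstract bases it on "possible occurrences of SAEs based on radiographic imaging, blood tests, and physical examinations"; the Results section says it is "assessed by closely monitoring possible occurrences of AEs or SAEs".

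**The concern.** Intensity describes how strong an event is. Seriousness describes what it leads to, for example readmission, reoperation or lasting impairment. A rule that derives one from the other can err both ways: an infection of moderate intensity that leads to readmission could be recorded as nonserious, and intense pain that settles by itself could be recorded as serious.

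The AE definition adds a second problem. Whether an event was expected is a property to record about it, not a condition for counting it. Limiting the count to patients who received the graft also leaves open what happens to harm from the fat harvest, which is part of the procedure under study.

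No statistical analysis is planned and there is no data safety monitoring board, so the conclusion rests on how individual events are classified. Three rules use that classification: the verdict that one SAE makes the combination not yet safe, the reporting deadlines (24 hours to the sponsor, 3 days to the ethics committee), and termination for an SAE involving severe graft-related toxicity or infection.

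**Working it through.** The article gives no event rate, error rate or precision target, so there is no figure of its own to reproduce beyond the sample size of 8. The check is mainly a comparison of sections.

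**1. Seriousness**

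| Section | What it implies |
|---|---|
| AE Assessment | serious or nonserious follows from intensity |
| Abbreviations | the S stands for severe |
| Study Design | the S stands for serious |
| Safety Assessment (Evaluation Methods) | one SAE decides the verdict |

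The first two rows agree with each other and conflict with the third. The fourth makes the conflict matter.

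**2. Scope of an AE**

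| Section | What it implies |
|---|---|
| AE Assessment, definition | only unexpected changes, in patients given the graft |
| Recruitment | six complications are disclosed in advance: bleeding, infection, cheek asymmetry, duct injury, nerve-branch injury, nonclosure |
| AE Assessment, termination sentence | infection linked to the graft can be an SAE |
| Safety Assessment | events resolved with analgesics or antibiotics are AEs |
| Sample Size | no AE or SAE is assumed to occur |
| Interventions | fat is taken from both cheeks; this is described before graft placement |

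Read literally, the definition can exclude an event disclosed in advance. The termination sentence and the Safety Assessment point the other way. Two assessors following the same text could therefore count the same event differently. A patient whose fat is harvested but who is not grafted falls outside the definition altogether.

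**3. Scale at n = 8**

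One patient is 1/8 = 12.5 percentage points. The SAE verdict changes only when the count moves between 0 and at least 1.

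As an illustration, let p be the per-patient probability of a foreseeable complication and f the share of such events removed by the word unexpected. Both are assumed, and patients are taken as independent. Then

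P(at least one counted among 8) = 1 − (1 − p(1 − f))^8.

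For p = 0.20 and f = 0: 1 − 0.80^8 = 0.832. For p = 0.20 and f = 0.5: 1 − 0.90^8 = 0.570.

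| Assumed p | f = 0 | f = 0.5 | f = 1 |
|---|---|---|---|
| 10% | 57% | 34% | 0% |
| 20% | 83% | 57% | 0% |
| 30% | 94% | 73% | 0% |

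Over this range, a clean AE count could owe as much to the definition as to the treatment. The column f = 1 is the strictest reading, not the likely practice.

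**The case against.** The case for leaving the text alone has several parts.

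- **A disclosed risk is not an expected event.** The Sample Size section assumes no events, so on the protocol's own terms any complication is unexpected. The references to infection, analgesics and antibiotics suggest that foreseeable events were meant to count. This stands as to intent. A reader might infer that all six disclosed complications are excluded; the documents do not support that, and for infection they contradict it. What remains is a definition that conflicts with its own use.
- **The graft condition may say whose events count, not when counting starts.** This stands. A reader might infer that everything before graft placement is ignored, but that is only one reading. Harvest without grafting is also unlikely within a single operation. The definition still leaves that patient out.
- **The WHO classification is not shown.** Its criteria might limit misclassification, so the examples above are possibilities, not certainties. The article's own sentence nevertheless names intensity as the basis.
- **Everything is recorded anyway, and Clavien-Dindo is used.** True, and it makes repair easy. The verdict, however, uses AEs and SAEs, not the medical history, and Clavien-Dindo is not linked to seriousness.
- **The abstract's SAE-only outcome and the abbreviation are slips.** The outcome difference is minor: the abstract's conclusion, Study Design, Results and Discussion all refer to both AEs and SAEs. The abbreviation matters only because it repeats the intensity rule.

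**Conclusion.** The point holds as a defect in two stated definitions. Deciding seriousness by intensity can misclassify events in either direction, and the restriction to unexpected changes in grafted patients can leave events uncounted and contradicts the article's other sentences. Because the article states these rules itself, they are not details left to a fuller document.

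The size is bounded by n = 8: 12.5 points per patient, and an SAE verdict that depends on zero versus at least one. The probabilities shown rest on assumed rates and an assumed filter; no figure in the article depends on them.

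A reader might infer two further things that the documents do not support. One is that the trial is tilted toward a finding of safety because the autologous-bone comparison would count the omitted events. The article gives neither the source of that comparison nor its AE definition, and the intensity rule can also push the verdict toward not yet safe. The other is that any single reclassified event flips the verdict. Omitting a nonserious AE leaves the SAE rule untouched.

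**What to change.** - **AE Assessment, AE definition:** any untoward medical occurrence, expected or not, from the start of surgery (including fat harvest), in every patient in whom surgery starts. Record expectedness as a separate attribute.
- **AE Assessment, SAE definition:** use outcome-based seriousness criteria. Record intensity and Clavien-Dindo grade as separate attributes that do not decide seriousness.
- **Abbreviations:** change severe to serious.
- **Abstract and Results:** state the primary outcome in the same words, covering AEs and SAEs up to 6 months.
- **Posttrial Care:** keep recording AEs through the additional 3 years, so that the 6-month cut-off defines the primary analysis and does not end AE capture.
- **Reconcile** AE Assessment, Recruitment and Safety Assessment, so that a disclosed complication is treated the same way in each.

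The cost is an amendment and some re-coding of 8 patients' records, for which the health changes should already be in the medical histories. The reported AE count may rise. The trial is already in follow-up, so the change should be dated, explained and made before the safety verdict is drawn.
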